### Recruitment

Participants from the community of São Carlos, Brazil, will be invited to participate in this study. Three main methods will be used to recruit potential participants: advertisements will be placed in local newspapers, magazines, and social media. Potential participants will be invited to complete a phone interview to pre-screen their eligibility to ensure that they meet the study selection criteria prior to randomization. If deemed eligible, an appointment will be scheduled to confirm eligibility, sign the ICF, and complete baseline evaluations.

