### Sample

To determine the sample size, the data of thigh interMAT from the study of Griessmann et al. (2014) were considered [55]. 16 participants per group was stipulated through a two-tailed hypothesis test, with a 5% level of significance and 80% test power.

Considering the possible sample loss in the course of the study, 20 subjects each, totaling 60 participants of either sex will be included in this study.

To be eligible, participants will be required to fulfill the following criteria:i.Aged between 40 and 65 years;ii.KOA clinically diagnosed fulfilling the American College of Rheumatology classification criteria of knee pain on most days of the past month and radiographically, classified as grades 2 or 3 according to Kellgren and Lawrence criteria [56].iii.Knee pain for ≥3 months;iv.Overall average knee pain in the last week ≥4 on a 0 to 10 Visual Analogue Scale (VAS).

The exclusion criteria are:i.Knee surgery;ii.Body mass index (BMI) ≥30 kg/m^2^;iii.Previous history of lower limb trauma;iv.Physical therapy, chiropractic, or acupuncture treatment or exercises specifically for the knee within the previous 6 months;v.Walking more than 30 min continuously daily or participating in a regular (more than twice a week) exercise program;vi.Current or past (within 3 months) oral or intra-articular corticosteroid use;vii.Systemic arthritic conditions such as rheumatoid arthritis;viii.Inability to walk unaided as this is necessary for some of the physical testing;ix.Medical condition precluding safe exercise such as uncontrolled hypertension, heart condition, cardiac pacemaker use, chronic diseases, impaired renal function, or any other medical condition that precludes participation in the study [57, 58];x.History of severe muscular lesions (above grade I);xi.Motor impairment due to neuromuscular diseases;xii.Cognitive deficits that compromise understanding of the tests;xiii.Starting any other exercise protocol or physical therapy during the study.xiv.Unable to comply with the protocol such as inability to attend therapy session or attend assessment appointment at the University.xv.Kellgren and Lawrence grades 0, 1, and 4.

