**Fig. 1 Fig1:**
[figure not shown]
Timeline of study procedure; EM: Educational meeting sessions; DXA: dual X-Ray absorptiometry; MVIC: maximal voluntary isometric contraction

On day 1, participants will be guided and familiarized with the experimental procedures to be performed. An evaluation form (personal and anthropometric data, blood pressure, knee pain, and previous medical history) and the informed consent form will be completed. During the same visit, the body composition test (Dual Energy X-ray Absorptiometry - DXA) will be performed and the participant will receive a referral for the knee radiographic exams.

Day 2 will be scheduled after the OA radiographic diagnosis and classification. During this visit, the WOMAC *(Western Ontario and McMaster Universities)* and Pain Catastrophizing Scale (PCS) questionnaires will be completed. Subsequently, the participants will perform three functional performance-based tests (40 m fast-paced walk test, 30 s chair stand test, and stair climb test), and the strength test*.* The functional performance tests and the strength test will be performed in random order. Participants will then receive the referral and guidelines for the computed tomography exam for thigh composition (adipose tissue and muscle mass) analysis and blood and urine samples will be collected for inflammatory and collagen activity marker analysis, identifying the systemic responses to exercise. After the baseline evaluations (Days 1 and 2), participants will be randomized through a randomization website (https://www.random.org/) into three groups: periodized circuit training, strength training, and educational protocol. The group distribution will be balanced for: number of males and females, age, body mass index (BMI), and radiographic severity. A researcher not involved with the evaluations and intervention sessions will be in charge of conducting the participant randomization and balance distribution. During and at the end of the 14 weeks intervention protocols, follow-up evaluations will be scheduled (Fig. 1).

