Data collections will be performed over the 14 weeks of the study. At baseline and post 14 weeks intervention (follow up) the following will be performed: computed tomography of thighs, maximal voluntary isometric contraction (MVIC), performance-based tests, blood and urine samples, questionnaires, and DXA. In the 5th, 10th, and 14th weeks, blood and urine samples will be collected for sCOMP and uCTX-II analysis and the MVIC test will be conducted.

All analyzes will be performed for all groups blindly, i.e., the evaluator of the collected data will be blinded to the group allocation.

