#### Application of the periodized circuit training protocol

The circuit training protocol will be conducted in three sessions per week for 14 weeks, totaling 42 exercise sessions. The minimum percentage of sessions that the participants is required to attend is 75% of the total sessions. Each session will consist of: warm-up exercises for 5 min, CT, and cool-down for 5 min with global stretching exercises. Initially, participants will be asked for their perception of pain or discomfort through a visual analogue scale (VAS) and will be instructed to inform the location of the pain through the Nordic questionnaire musculoskeletal symptoms; baseline blood pressure (BPi) and initial heart rate (HRi) will also be measured. Subsequently, the participants will perform a warm-up exercise for 5 min on a stationary bicycle with minimum resistance.

Immediately after the warm-up exercise, each participant will perform the circuit training protocol. The participants will be instructed to perform each exercise as fast as possible, with the maximum number of repetitions during the established time in each training phase (light, moderate, and intense). The first station of exercises to be performed will be defined in a random order at each session. After the end of the first exercise station, the participant will move to the next exercise station, following a specific order to allow different muscle groups to alternate between rest and work, favoring recovery and minimizing the risk of muscle fatigue [34] as shown in Fig. 2.

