### Educational protocol

The educational protocol will follow the model proposed by Messier et al. (2013b), in order to provide care, social interaction, and health education [2]. Meetings of 60 min will be held twice a month for 14 weeks, totaling 8 meetings. Interactive presentations will be performed addressing topics such as pathophysiology of osteoarthritis, and American College of Rheumatology (ACR) recommendations on nutrition, posture, and lifestyle. In addition, at the end of the meetings, participants will perform the same stretching exercise as performed in the exercised intervention protocols, but only on the upper body for five minutes, in order to improve adherence and increase the perceived benefits. According to the authors, there is no evidence that this practice of health education can directly influence the primary results of the present study [2]. Participants in the trained groups will also participate in the education and health sessions at separate times.

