### Statistical analysis

Data analysis will be performed using the software *Statistical Package for the Social Sciences* version 20.0 (*SPSS* Inc., Chicago, IL, USA). An intention to treat analysis will be conducted for all data analyses. Initially, descriptive analysis of variables will be performed as mean, standard deviation, and coefficient of variation. Next, normality and homogeneity of variance will be checked by the Kolmogorov-Smirnov test and Levene’s test, respectively**.** If normal distribution of data is not observed, the same transformations will be carried out, to allow the application of parametric tests**.**

Two-way ANOVA (group X time) will be conducted for the dependent variables. When significant differences were observed in the group or interaction, will be performed a post-hoc Bonferroni Test. For all measured variables, the estimated sphericity will be examined in accordance with Mauchly’s W Test, and the Greenhouse-Geisser correction will be used as needed. For comparison between moments, for uCTX-II, sCOMP, and MVIC repeated measures ANOVA (baseline X during protocols X follow-up) will be performed. When significant main effects are found, the Bonferroni test will be used to identify statistical differences. For IL1-β, IL-6, TNF-α, leptin, adiponectin, WOMAC, PCS, DXA, computed tomography, and functional performance-based tests, the t-test will be used (baseline X follow-up). For all analyzes a significance level of 5% will be adopted (*p* < 0.05). No interim efficacy or subgroup analyses are planned.

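### Exclusion criterion xiii names an event that can occur almost only after randomisation and, applied as written, contradicts the stated intention-to-treat analysis

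*Protocol article*

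**What the plan says.** Four parts of the protocol article bear on this.

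- **Sample, exclusion criteria.** Item xiii reads "Starting any other exercise protocol or physical therapy during the study". It is worded identically for all three arms. Earlier items already cover past and current behaviour: item iv excludes recent physical therapy and knee-specific exercise (previous 6 months), and item v excludes "Walking more than 30 min continuously daily or participating in a regular (more than twice a week) exercise program".
- **Recruitment and Procedures.** Potential participants are pre-screened by phone "to ensure that they meet the study selection criteria prior to randomization", and eligibility is then confirmed at an appointment. Allocation comes next: "After the baseline evaluations (Days 1 and 2), participants will be randomized through a randomization website". The text under Fig. 1 treats the study period as the intervention period: "Data collections will be performed over the 14 weeks of the study".
- **Statistical analysis.** "An intention to treat analysis will be conducted for all data analyses".
- **Educational protocol.** The control arm receives lectures and brief upper-body stretching: "Meetings of 60 min will be held twice a month for 14 weeks, totaling 8 meetings". Both training arms have three sessions a week, 42 in all.

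The article does not say what happens to a randomised participant who meets item xiii: whether the intervention stops, follow-up stops, or the data leave the analysis.

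**The concern.** An exclusion criterion decides who enters a trial. Item xiii describes future conduct, so someone who is eligible at screening and randomised can become excluded weeks later. If acted on, it removes people for behaviour that their allocation may influence, and the groups compared are then no longer the groups that were randomised.

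The contrasts most exposed are circuit training versus education and strength training versus education. Participants enter with knee pain of at least 4 out of 10 and no regular exercise programme, and they necessarily know whether they have been given training. Those allocated to education could plausibly look for exercise or physical therapy elsewhere more often. If those who do so improve, removing them makes the remaining controls look worse and widens the contrast. Leaving the two statements unreconciled also allows the choice between them to be made after uptake is known.

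**Working it through.** **1. When can item xiii be met?** Set the sections in time order: phone pre-screen, eligibility appointment and consent, Days 1 and 2 baseline evaluations, randomisation, 14 weeks of intervention with follow-up. Starting another programme during the study can precede randomisation only in the short gap between consent and allocation. An exclusion in that gap would be legitimate. In the remaining 14 weeks the event follows allocation. Items iv and v already deal with past and current treatment, so what xiii adds is future behaviour, which no screening visit can verify.

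**2. Can it coexist with intention to treat?** A participant who starts physical therapy in week 6 is excluded under xiii and analysed as randomised under the Statistical analysis section. Both cannot hold.

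**3. The plan's own sample size.** The Sample section states 16 per group (two-sided 5%, 80% power), raised to 20 per group and 60 in total for loss. It gives no effect size or SD, so 16 cannot be reproduced directly. Solving backwards:

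- Normal approximation: d = (1.960 + 0.842) × √(2/16) = 0.99 SD.
- t-test: d = 1.02 SD.
- Loss step: 16 / (1 − 0.20) = 20, and 3 × 20 = 60. Both agree with the text and imply an allowance of 4 per arm.

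No stated figure is disputed. The value 1.02 SD serves only as a yardstick.

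**4. Size of a possible bias (assumed inputs).** Let a share q of controls start outside exercise or therapy, with a mean outcome g SD better than the other controls. Writing μ for the mean of the others, the full control mean is better than μ by q × g. After exclusion it is μ. The shift is therefore q × g:

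| q | g (SD) | shift (SD) | share of 1.02 SD |
|---|---|---|---|
| 0.10 | 0.3 | 0.03 | 3% |
| 0.15 | 0.5 | 0.075 | 7% |
| 0.25 | 0.8 | 0.20 | 20% |

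If those who seek therapy are the ones doing worse, g is negative and the same shifts narrow the contrast.

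**5. Loss of numbers (assumed uptake).** With 20 controls, fewer than 16 remain if 5 or more are excluded. The binomial probability is 4%, 37% or 76% for uptake of 10%, 20% or 30%. At d = 1.02 and with no other loss, two-group power is 88% for 20 versus 20, 84% for 20 versus 16 and 77% for 20 versus 12. Power falls modestly, so possible bias is the larger issue.

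**The case against.** The strongest reply is that nobody is shown to be removed. The only explicit analysis rule is intention to treat, and the Recruitment section places the eligibility check before randomisation. Item xiii sits next to xiv, which concerns inability to comply with the protocol and is a forward-looking judgement of suitability. On that reading, xiii is loose wording for a participant who intends to start other treatment. This stands in part: what the document contains is an unreconciled contradiction, and removal is not confirmed. It does not dispose of the point, because xiii as worded refers to starting a programme and not to planning one.

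Three stronger readings are tempting and are not supported.

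- **That xiii selectively removes controls.** It applies equally to all arms, and no uptake by arm is given. The educational meetings and stretching are also meant to support adherence and perceived benefit. Heavier loss from that arm is a plausible inference only.
- **That the bias must favour circuit training.** Dropping education participants does not affect circuit versus strength, which is one of the stated hypotheses. Even against education, the sign depends on whether those who start other treatment do better or worse than the rest.
- **That the 75% attendance requirement also breaks intention to treat.** The circuit section states "The minimum percentage of sessions that the participants is required to attend is 75% of the total sessions" (0.75 × 42 = 31.5 sessions) but attaches no consequence to missing it. An attendance target is compatible with intention to treat. Its absence from the strength section may only reflect a condensed article.

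The full protocol or analysis plan may define deviations and analysis sets. Their absence here is not the complaint. The complaint is that two published statements conflict.

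**Conclusion.** The point holds in a limited form. Item xiii makes a mainly post-randomisation event a ground for exclusion, cannot be checked at screening, and contradicts the intention-to-treat statement if applied as written. The conflict rests on the text alone and needs no assumption.

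The consequence does rest on assumptions. With 10% to 25% uptake among controls and an outcome 0.3 to 0.8 SD better in those who take it up, excluding them shifts the control mean by 0.03 to 0.20 SD, roughly 3% to 20% of the difference implied by 16 per group. Neither range comes from the document, the upper end is generous for a programme begun part-way through 14 weeks, and the sign could reverse. The sample size and the attendance requirement are not at fault.

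**What to change.** Reconcile the Sample and Statistical analysis sections with two changes.

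1. Reword item xiii so that it can be judged at screening: currently in, or planning to start, another exercise or physical therapy programme.
2. State that starting such a programme after randomisation is recorded as a protocol deviation in all three arms, and that the participant stays in follow-up and is analysed in the allocated group. A short addition can say that low attendance likewise removes nobody from the intention-to-treat analysis.

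These changes concern eligibility wording and analysis only. They leave the interventions and the planned 20 per arm, 60 in total, unchanged. The cost is a brief amendment, the recording of outside exercise and therapy in every arm, and possibly a slightly smaller effect estimate, because controls who take up exercise stay in the comparison.

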### Procedures

All experimental procedures will be performed following the timeline shown in Fig. 1. The evaluations will be conducted at the Articular Function Analysis Laboratory (LAFAr) and the training protocols will be conducted at the Physical Therapy Department of the Federal University of São Carlos (UFSCar), in a room with a controlled temperature (between 21 °C and 23 °C).

**Fig. 1 Fig1:**
[figure not shown]
Timeline of study procedure; EM: Educational meeting sessions; DXA: dual X-Ray absorptiometry; MVIC: maximal voluntary isometric contraction

On day 1, participants will be guided and familiarized with the experimental procedures to be performed. An evaluation form (personal and anthropometric data, blood pressure, knee pain, and previous medical history) and the informed consent form will be completed. During the same visit, the body composition test (Dual Energy X-ray Absorptiometry - DXA) will be performed and the participant will receive a referral for the knee radiographic exams.

Day 2 will be scheduled after the OA radiographic diagnosis and classification. During this visit, the WOMAC *(Western Ontario and McMaster Universities)* and Pain Catastrophizing Scale (PCS) questionnaires will be completed. Subsequently, the participants will perform three functional performance-based tests (40 m fast-paced walk test, 30 s chair stand test, and stair climb test), and the strength test*.* The functional performance tests and the strength test will be performed in random order. Participants will then receive the referral and guidelines for the computed tomography exam for thigh composition (adipose tissue and muscle mass) analysis and blood and urine samples will be collected for inflammatory and collagen activity marker analysis, identifying the systemic responses to exercise. After the baseline evaluations (Days 1 and 2), participants will be randomized through a randomization website (https://www.random.org/) into three groups: periodized circuit training, strength training, and educational protocol. The group distribution will be balanced for: number of males and females, age, body mass index (BMI), and radiographic severity. A researcher not involved with the evaluations and intervention sessions will be in charge of conducting the participant randomization and balance distribution. During and at the end of the 14 weeks intervention protocols, follow-up evaluations will be scheduled (Fig. 1).

Data collections will be performed over the 14 weeks of the study. At baseline and post 14 weeks intervention (follow up) the following will be performed: computed tomography of thighs, maximal voluntary isometric contraction (MVIC), performance-based tests, blood and urine samples, questionnaires, and DXA. In the 5th, 10th, and 14th weeks, blood and urine samples will be collected for sCOMP and uCTX-II analysis and the MVIC test will be conducted.

All analyzes will be performed for all groups blindly, i.e., the evaluator of the collected data will be blinded to the group allocation.

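### Allocation is balanced on four factors, but the group x time ANOVA adjusts for none of them and uses baseline only as a time level; a baseline-adjusted ANCOVA would be more efficient at almost no cost

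*Protocol article*

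**What the plan says.** Under Procedures, once the two baseline visits are complete, "participants will be randomized through a randomization website" into three arms. The same paragraph adds: "The group distribution will be balanced for: number of males and females, age, body mass index (BMI), and radiographic severity". The task is given to an independent person: "A researcher not involved with the evaluations and intervention sessions will be in charge of conducting the participant randomization and balance distribution".

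Under Statistical analysis the between-group model is stated outright: "Two-way ANOVA (group X time) will be conducted for the dependent variables". The abstract describes the same comparison, with baseline and follow-up as levels of the time factor. Neither place names a covariate. The Bonferroni post-hoc test may follow a significant group effect or a significant interaction.

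The size of the trial is set under Sample: "16 participants per group was stipulated through a two-tailed hypothesis test, with a 5% level of significance and 80% test power". It is then raised to "20 subjects each, totaling 60 participants of either sex". InterMAT is declared primary under Thigh computed tomography, and Procedures schedules the scan at baseline and after the 14 weeks only.

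**The concern.** Factors considered important enough to balance the arms are normally carried into the model. If they predict the outcome and are left out, their variation stays in the error term although the design has already removed it from the comparison of arms. The stated standard error is then larger than the true one. Separately, entering baseline as a time level forces a comparison of raw change, whereas a covariate lets the data set how much of the baseline value is subtracted.

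With a planned power of 80% at 16 completers per arm, there is little precision to spare. The post-hoc rule adds a further weakness: a group main effect over two visits averages a pre-treatment value with a post-treatment one, so it dilutes any intervention effect and also picks up chance differences at baseline.

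**Working it through.** **Inputs from the article.** Three arms; 16 per arm at two-sided 5% and 80% power, raised to 20 (Sample); two CT visits (Procedures); Kellgren-Lawrence grade 2 or 3 only (Sample), so grade needs one indicator.

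**Inputs not in the article, assumed here.** The baseline to follow-up correlation r of interMAT, taken as 0.5 to 0.9; the share of the variance of change explained by the four factors, taken as 0 to 30%; equal variance σ² at both visits; one interMAT value per participant per visit. The reliability of 0.973 under Thigh computed tomography concerns re-reading scans one week apart and cannot stand in for r over 14 weeks.

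**1. The plan's own figure.** The 16 per arm cannot be reproduced, because no difference or SD is printed. Solving backwards for two arms:

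d = (1.960 + 0.842) × √(2/16) = 2.802 × 0.3536 = 0.99 (1.02 with the t distribution).

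The step to 20 fits a 20% loss, 16/(1 − 0.20) = 20, though no rate is given. Below, 16 per arm is taken to give 80% power for the change-score comparison.

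**2. Change score against ANCOVA.** With two visits the group x time interaction is the test on change.

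- Variance of change: 2(1 − r)σ²
- Residual variance after adjusting for baseline: (1 − r²)σ²
- Ratio: (1 − r²)/[2(1 − r)] = (1 + r)/2
- Power at 16 per arm: Φ(2.802/√ratio − 1.960). At r = 0.5 this is Φ(3.24 − 1.96) = Φ(1.28) = 90%.

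| r (assumed) | Variance ratio | Extra participants the change score needs (1/ratio − 1) | n per arm for 80% with ANCOVA | ANCOVA power at 16 per arm |
|---|---|---|---|---|
| 0.5 | 0.75 | 33% | 12 | 90% |
| 0.7 | 0.85 | 18% | 14 | 86% |
| 0.9 | 0.95 | 5% | 16 | 82% |

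**3. Leaving out the balancing factors.** Simulated trials had 60 participants in three arms, allocated by minimisation with a random element on four two-level factors of 50% prevalence, with no treatment effect. There were 3,000 runs per row, so the simulation error near 5% is √(0.05 × 0.95/3000), about 0.4 points. The power columns use the noncentral t with 48 completers (44 residual degrees of freedom without the factors, 40 with them). They hold the error SD at its step 1 value, so the gain in step 2 is not counted again.

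| Share of variance of change explained (assumed) | Type I error, unadjusted | Type I error, adjusted | Power without factors | Power with factors |
|---|---|---|---|---|
| 0% | 5.3% | 5.3% | 78% | 78% |
| 10% | 3.7% | 4.5% | 78% | 82% |
| 20% | 3.1% | 5.3% | 78% | 86% |
| 30% | 1.9% | 5.1% | 78% | 90% |

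**4. The group main effect as a trigger.** An effect δ at follow-up becomes δ/2 in the mean of the two visits, whose variance is (1 + r)σ²/2. Relative to the interaction, the standardised effect shrinks by √[(1 − r)/(1 + r)].

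- r = 0.5: 2.802 × 0.577 = 1.62; Φ(1.62 − 1.96) = 37%
- r = 0.7: 2.802 × 0.420 = 1.18; Φ(1.18 − 1.96) = 22%
- r = 0.9: 2.802 × 0.229 = 0.64; Φ(0.64 − 1.96) = 9%

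The interaction has 80% in each case.

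**5. Degrees of freedom.** Baseline, sex, age, BMI and grade take one each. With 48 completers the residual falls from 48 − 3 = 45 to 40; with all 60 it falls from 57 to 52.

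**The case against.** The strongest reply is that the planned test is sound. Under randomisation a change-score comparison is unbiased and holds its level. Stable differences between participants linked to sex, age, BMI or grade already cancel in the change. The article offers no evidence that these factors predict change in interMAT; if they explain none of it, step 3 shows no gain. If interMAT is very stable over 14 weeks, the gain in step 2 is also small. All of this stands, and it limits the point to efficiency.

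It does not remove the point. The article states a model rather than leaving one to a fuller document. That model is applied to all the dependent variables, including questionnaires, cytokines and performance tests, whose correlations over time may be lower than that of interMAT.

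Three stronger readings are tempting and are not supported:

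- **Baseline is ignored.** It is not. It is a level of the time factor, and the interaction is built on change from it.
- **The named website cannot deliver the balance.** The article does not describe what the site can do, and it assigns the balancing to a researcher. An unrestricted draw of 60 would give exactly 20/20/20 with probability 60!/(20!³ × 3⁶⁰) = 1.4%. That describes a procedure at odds with the planned 20 per arm, so it does not count against the plan.
- **The researcher balances the arms by hand.** No manual reassignment is described. Stratified lists or minimisation would fit the same words, and an article may leave the algorithm to the full protocol.

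**Conclusion.** The point holds as one of efficiency and of agreement between design and analysis. It is not a point of validity. The change-score test loses 5% to 25% of variance against ANCOVA for r between 0.9 and 0.5, which equals about 5% to 33% more participants. The article gives no r, so the place within that range is unknown.

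A reader might infer that omitting the balancing factors always inflates the standard errors or raises false positives. Neither follows. The loss arises only to the extent that the factors predict change, and the direction is conservative: about 3.7% actual type I error at 10% explained and 1.9% at 30%, under the simulated minimisation.

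The least defensible element is the group main effect as a trigger for post-hoc testing. Under the same assumptions it has 9% to 37% power where the interaction has 80%. The change is worth making because it uses only data the trial already collects.

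**What to change.** State the primary between-group analysis of interMAT as an ANCOVA of the 14-week value on group, baseline interMAT, sex, age and BMI (both continuous) and Kellgren-Lawrence grade. Take the three pairwise group contrasts from that model with Bonferroni adjustment, and remove the group main effect of the two-way ANOVA as a trigger. Use the same form for the other outcomes measured at baseline and follow-up, each with its own baseline value.

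The cost is a change of wording and about five degrees of freedom out of 45 with 48 completers; no new data are needed.

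On allocation, at most ask the investigators to state the algorithm by which balance on the four factors is achieved.
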